# Methods: Assignment of interventions (for controlled trials)

## Allocation

### 16a. Sequence generation

Clusters (health facilities) will be stratified according to country (Kenya and South Sudan) and then randomly assigned to the intervention or control group according to a computer-generated allocation sequence.

### 16b. Implementation

The research coordinator in each country will conduct the randomization exercise, and will inform the research teams after the interventions are assigned. Participants will be enrolled by the research officer located at each health facility. Health facilities will be randomized, not individuals.

## Blinding (masking)

There will be no blinding in this trial as it is not logistically possible.

# Methods: Data collection, management, and analysis

## Data collection methods

### 18a Plans for assessment and collection of outcome, baseline, and other trial data

A dedicated research officer will be based at each health facility for the entire duration of the study. All research officers will be given a two week training prior to study inception. They will be required to pass an exam after training is complete to test protocol knowledge, anthropometric measurement techniques (weight, height, and MUAC measurements and oedema assessment), data management techniques and coaching and counselling methodologies.

Each research officer will oversee the training and supervision of health facility staff, enrolment and treatment of children according to the study protocol and data management. S/he will conduct initial and refresher trainings with health facility staff as well as have continuous on the job trainings. They will assess the accuracy of anthropometric measurements taken by health facility staff and review the patient cards and registers on a daily basis to ensure data quality.

The information below will be collected in addition to the patient cards used in each country. MoH OTP cards will be used for all participants in the Combined Protocol. MoH OTP or SFP cards (as applicable) will be used for all participants in the Standard Protocol. Forms will be pilot tested and where needed adjusted prior to the start of the main study.

1. **Admission** (in addition to the patient card)

- Mother is caretaker (yes/no)
- Father lives in home (yes/no)
- Maternal educational achievement (none, primary, secondary)
- # children <5 in household
- Access to toilet
- Water source
- Breastfeeding in last 24 hours (yes/no)
- Livelihood/main source of income
- Other sources of free food (blanket feeding, general food distribution, etc)
- Household Hunger Score:
  - Was there ever no food to eat of any kind in your house?
  - Did you or any household member go to sleep at night and there was not enough food?
  - Did you or any household member go a whole day without eating anything at all because there was not enough food?

1. **Weekly** (in addition to the patient card) :
   - Presence of morbidity since last visit (diarrhea, vomiting, fever, cough)- *SFP*
   - Referral for medical evaluation since last visit
   - Breastfeeding in last 24 hours (yes/no)
2. **Discharge** (in addition to the patient card)
   - Breastfeeding in last 24 hours (yes/no)
   - Questions to assess opportunity cost of accessing treatment to contribute to the cost-effectiveness analysis
3. **SQUEAC** (after completion of final enrolment)

A Semi-quantitative evaluation of access and coverage (SQUEAC) will be conducted at the mid-point of the trial to assess coverage in each health facility catchment area. The SQUEAC methodology has been validated by the Coverage Monitoring Network (CMN) and is the preferred coverage assessment methodology for comparison across nutrition programs. ComPAS will use a consultant from the CMN to lead the SQUEAC coverage surveys in both Kenya and South Sudan. The results will be per health facility catchment area. The coverage surveys will be based on a MUAC-only definition of Global Acute Malnutrition (GAM (MUAC<125mm). Weight and height measurements will not be taken.

The numerator/denominator for the SQUEAC coverage survey will be:

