## Interventions

### 11a. Interventions for each group

Table 2: Combined Protocol Intervention: Kenya and South Sudan

| **Combined Protocol** |  |
| --- | --- |
| **Admission Criteria** | <125mm MUAC  AND/OR bipedal oedema (+)  AND clinically uncomplicated (i.e. passes appetite test, no Integrated Management of Childhood Illness (IMCI) danger signs/ no serious medical complications) |
| **Treatment Frequency** | <115mm: Weekly  115-<125mm: Bi-weekly |
| **Dosage** | <115mm and/or oedema (+): Two 92g sachets RUTF/day (1000 kcal/day)  115-<125mm : One 92g sachet RUTF/day (500 kcal/day) |
| **Transition from 2 RUTF to 1 RUTF:** | Two consecutive weekly measurements at or above 115mm and no oedema |
| **Cured** | ≥125mm for 2 consecutive measurements and no oedema, with 3 week minimum stay |
| **Default** | Absent for 3 consecutive visits |
| **Non-recovered** | Has not achieved discharge criteria within 16 weeks |
| **Discharge procedures** | Discharge ration of 7 RUTF sachets |
| **Routine medical treatments (as per national protocol):** | For all children with MUAC <115mm and/or bipedal oedema (+) on admission:   - **Amoxicillin:** Give first dose at health facility and then give remainder to caretaker with instructions to give twice daily for 7 days   For all children with MUAC <125mm and/or bipedal oedema (+) on admission:   - **Malaria**: according to national protocol - **Measles:** one vaccine on 4^th^ visit (4^th^ week) (children >6 months) (unless already vaccinated) - **Deworming:** one dose (albendazole or mebendazole) on the second visit (second week) (children >1 year) |
| **Referral Procedures (as per national protocol)** | Any child who develops medical complications and/or is not responding to treatment will be referred for a medical evaluation and/or to the Stabilization Center.  ‘Not responding to treatment’ will be defined in the following way:   - Failure to gain any weight (non-oedematous children) - Failure to start to lose oedema - Oedema still present - Weight loss since admission to program (non-oedematous children) - Failure of appetite test - Weight loss of 5% of body weight - Weight loss for two successive visits |

Table 3- Standard Protocol Intervention- Kenya

| **Standard Protocol- Kenya** | **OTP** | **SFP** |
| --- | --- | --- |
| **Admission Criteria** | - WHZ < -3   And/or   - MUAC < 115mm   And/or   - Bilateral pitting oedema (+/++) | - Discharged from OTP   And/or   - WHZ <-2 to WHZ >-3  and/or - MUAC 115mm < 125mm |

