### 11d. Relevant concomitant care and interventions that are permitted or prohibited during the trial

Routine health care that can be treated on an outpatient basis will be provided to all children per the national CMAM protocol. Any child with a medical complication and/or not responding to treatment will be referred to the Stabilization Center for a medical evaluation. Inpatient care will be offered to those who require it for as long as needed. If a child is admitted for inpatient care, they will be discharged as a referral and exit from the study.

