## Outcomes

Table 6: Primary and Secondary Outcomes

|  | **Measurement variable** | **Analysis metric** | **Method of aggregation** | **Time point** |
| --- | --- | --- | --- | --- |
| Primary | | | | |
| Recovery | MUAC ≥125mm and no oedema  Note: The definition of recovery in both the control and intervention groups will be defined as two consecutive measurements with a MUAC≥125mm and no oedema. For the purposes of analysis, children receiving the standard protocol will be considered as cured when their MUAC≥125mm and no oedema for two consecutive measurements, even if they continue to receive treatment until they reach a WHZ >-2. | Final value | Proportion | End of treatment |
| Secondary | | | | |
| Coverage | % of children eligible for treatment (MUAC<125mm) who receive it  Note: The coverage surveys will be based on a MUAC-only definition of Global Acute Malnutrition (GAM (MUAC<125mm). Weight and height measurements will not be taken. | Final value | Proportion | Semi-quantitative evaluation of access and coverage (SQUEAC) survey (after final enrolment) |
| Defaulter | Child discharged as defaulter (3 missed visits) | Final value | Proportion | End of treatment |
| Died | Child died during treatment | Final value | Proportion | End of treatment |
| Length of stay | Days in treatment | Duration of time | Sum | End of treatment |
| Average daily weight gain | grams/kilograms/day | Daily | Mean | End of treatment |
| Average daily MUAC gain | mm/day | Daily | Mean | End of treatment |

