## Sample size

The primary outcome, ‘recovery’, in both the control and intervention groups will be defined as two consecutive measurements with a MUAC≥125mm and no oedema. We expect the recovery rate to be 85% based on the average program statistics in Nairobi, Kenya and Aweil East, South Sudan. If the combined protocol is non-inferior to the current protocol, allowing for a 10% non-inferiority margin, then we would require 12 clusters in each arm with 100 children in each cluster to demonstrate non-inferiority of the combined protocol, with 80% power at the 5% level of significance. An intracluster correlation coefficient (ICC) of 0.05 was used, a conservative estimate based on the results of a similar cluster randomized study testing an integrated SAM/MAM protocol in Sierra Leone (Maust et al. 2015).

In order to account for losses to follow-up (estimated as 15%) and cross-overs (estimated as 5% in each arm), 150 children per cluster will be recruited for inclusion in the study. This was determined based on the following calculation:

100 x 1/(1-.15) x (1/(1-.05-.05)²) = 146

Table 7: Sample Size Calculations

| **Assumptions** | **Value** |
| --- | --- |
| Power | .80 |
| Level of significance | .05 |
| Intervention recovery | .85 |
| Control recovery | .85 |
| Margin of Non-Inferiority | .10 |
| One or two-tailed test | 2 |
| Number of facilities per arm | 12 |
| **Individuals per cluster** | **100** |
| **Total individuals** | **2400 (1200 in South Sudan, 1200 in Kenya)** |

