### 18b. Plans to promote participant retention and complete follow-up

Participants will be given a careful explanation of the importance of completing treatment and have the opportunity to ask any questions prior to enrolment. As described in section 21, all participants will be given the contact information of two local representatives they can approach if they have any feedback for or wish to express any concerns at any time during the study. A health visitor (a community health worker) will follow-up patients who begin to default from treatment (after one week of missed treatment) to assess the reasons for defaulting and help the family strategize on ways to complete to treatment.

If a family chooses not to bring their child back to complete treatment, the child will be discharged as ‘defaulted’ after 3 weeks of missed treatment. No additional data will be collected on children who default.

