## Dissemination policy

### 28a Plans for investigators and sponsor to communicate trial results to participants, healthcare professionals, the public, and other relevant groups

The final trial results will be written into a final report and shared with the institutions described in section 27. The interpretation of results, implications and next steps will be discussed with the MoH in each country, the expert committee and the consultative committee before dissemination or publication at either national or international levels.

A presentation will be made at the Nutrition Information Technical Working Group and the Emergency Nutrition Advisory Committee in Nairobi, Kenya and at the MoH and Nutrition Cluster in Juba, South Sudan to review the finalized results with key national stakeholders and discuss next steps for dissemination and publication.

Results will also be shared with key global nutrition committees and working groups, including the Global Nutrition Cluster (GNC), the Emergency Nutrition Network (ENN) and the Nutrition Forum, among others.

An article for publication in a peer-reviewed journal will be prepared summarizing the key outcomes of the trial and the implications for nutrition program policy. A separate article will be prepared summarizing the key outcomes of the cost-effectiveness analysis.

A workshop will be organized within one year of the trial end date to present the finalized analyses and discuss the policy implications. The workshop will be open to all key stakeholders (Non Governmental Organizations(NGO), donors, the United Nations (UN), Ministries of Health, universities) involved in the ComPAS study.

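### The opportunity-cost questions are listed only at discharge, so families who default give no access-cost data to the cost-effectiveness analysis

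*Protocol*

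**What the plan says.** Section 18a sets out what is collected at each contact beyond the patient card. Under Discharge it lists "Questions to assess opportunity cost of accessing treatment to contribute to the cost-effectiveness analysis". The Admission list covers household and feeding items, including livelihood or main source of income, but not the cost of reaching the clinic. The Weekly list has no such item either.

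Section 18b says that when a family stops attending, "the child will be discharged as ‘defaulted’ after 3 weeks of missed treatment", and then: "No additional data will be collected on children who default". A community health worker visits after one missed week to ask about the reasons, but no cost questions are specified for that visit.

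Other exits are treated differently. Under section 11d, children admitted for inpatient care are recorded as follows: "they will be discharged as a referral and exit from the study". Table 6 records death as "Child died during treatment" and says nothing about a caretaker interview. Table 2 defines non-recovered as "Has not achieved discharge criteria within 16 weeks".

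Section 6a names cost-effectiveness among the goals of the Combined Protocol. Cost is not among the objectives in section 7 or the outcomes in Table 6. Section 28a says: "A separate article will be prepared summarizing the key outcomes of the cost-effectiveness analysis".

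**The concern.** A default is an administrative discharge, entered while the family is absent. With the questions tied to discharge and data collection ended by default, these families have no scheduled occasion on which to answer.

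The gap may be informative, because families for whom a visit costs most in fares, time or lost work are plausibly more likely to stop coming. Section 11c itself anticipates caretakers who have difficulty bringing the child to the clinic. An analysis plan can impute a missing cost, but it cannot recover answers that were never asked for, and section 18a lists no earlier access-cost measure to impute from.

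At stake is the access-cost input to the cost-effectiveness analysis, both its level and, if default differs by arm, its comparison between arms.

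**Working it through.** **Inputs from the protocol.** Section 14 gives 24 clusters, 150 children recruited per cluster and 15% loss to follow-up. The recruitment figure reproduces: 100 / (0.85 × 0.90²) = 145.2, rounded up to 146 and then set at 150.

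**Number without data.** 24 × 150 = 3,600 and 0.15 × 3,600 = 540. This takes all planned loss as default. The protocol does not break the 15% down, so 540 is an upper figure for default under that plan.

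**Inputs that are assumptions.** Let r be defaulters' cost per visit relative to families who answer, taken as 1.5 to 2. Let v be the share of a full course of visits that defaulters make, taken as 0.5 or 1. The protocol gives neither. The mean among families who answer is set to 1, and d is the share who default.

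**Per-visit cost.** The true mean, weighted by visits, is [(1 − d) + d·v·r] / [(1 − d) + d·v]. The shortfall of the observed mean is 1 − 1/true mean. With d = 0.15:

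| v | r | True mean | Understated by |
|---|---|---|---|
| 1 | 1.5 | 0.85 + 0.225 = 1.075 | 7.0% |
| 1 | 2 | 0.85 + 0.30 = 1.15 | 13.0% |
| 0.5 | 1.5 | 0.9625 / 0.925 = 1.041 | 3.9% |
| 0.5 | 2 | 1.00 / 0.925 = 1.081 | 7.5% |

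**Total cost per child.** The true mean is (1 − d) + d·v·r. At v = 0.5 and r = 2 it is 0.85 + 0.15 = 1.00, so there is no error. At v = 0.5 and r = 1.5 it is 0.9625, so the observed mean is too high. At v = 1 it is understated by the same 7.0% and 13.0% as above. The sign depends on whether v·r is above or below 1.

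**Between arms.** Take v = 1 and equal costs among answering families in both arms.

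- With 15% default in each arm and the same r, the true difference is zero and so is the observed one.
- With 10% v 20% default (an assumption) and r = 2, the true means are 0.90 + 0.20 = 1.10 and 0.80 + 0.40 = 1.20. The ratio is 1.20 / 1.10 = 1.09, so a 9% difference would show as none.

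**The case against.** The strongest case against is that the inputs behind any percentage are not in the protocol, and that this is one input to a separately reported analysis whose methods, including the handling of missing costs, may be set out elsewhere. The questionnaires and data-collection matrices are in an appendix and annex not available here, so the absence of an earlier question is checked only against the lists in section 18a. It is also natural to ask about the cost of a whole course of treatment at its end. All of this stands, and it limits the size and weight of the point. It does not supply answers from families who default.

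Several stronger readings are tempting, and the protocol does not support them.

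- A reader might infer that referred children and those who die are also never covered. Referral is itself a discharge under section 11d, and the text neither provides for nor rules out the questions then. On deaths it is silent.
- A reader might infer that only families who complete treatment successfully can answer. Non-recovered children also reach a discharge and their families can be asked.
- A reader might infer that the cost-effectiveness comparison rests on these answers. Section 18a says only that they contribute to it.
- A reader might infer that the trial predicts different default rates. Section 7 expects similar exit status and ties reduced loss between OTP and SFP to coverage. That is indirect support at most.

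There is one textual reason why default might differ by arm. Table 4 counts default after two missed visits in the South Sudan standard arm, while Table 2, section 11c and Table 6 say three. These passages need reconciling.

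**Conclusion.** The point holds for defaulters. Their access costs are not collected, and the missingness may depend on the cost itself. Up to about 15% of children (540 of 3,600) are concerned if planned loss is read as default.

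Per-visit access cost is probably understated, by about 4% to 13%. That range rests on an assumed cost ratio of 1.5 to 2 and on defaulters making between half and all of a full course of visits. It would be wrong to say flatly that opportunity cost is understated: for total cost per child the direction is uncertain and can reverse. The between-arm comparison is affected mainly if default differs by arm.

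This is a weakness in the collection schedule for a secondary economic analysis. The primary outcome and the outcomes in Table 6 are untouched.

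**What to change.** Add the per-visit access-cost questions (travel time, fare, waiting, work lost) to the Admission form or the first follow-up visit, identically in both arms. Asking at admission also reaches families who never return. Keep the discharge questions as an update. Compute each family's cost as per-visit cost times the visits on the patient card, so that defaulters contribute for the visits they made. State whether the questions are asked when a child is referred to inpatient care and after a death.

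The cost is a few minutes per family and a form change, and section 18a already provides for piloting and adjusting the forms before the main study. The downside is that an early answer forecasts later visits less accurately than recall at discharge, which is why the discharge update should stay.

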# of children who receive treatment for acute malnutrition/# of children eligible for treatment (<125mm MUAC)

1. **Qualitative end-line study** (focus group discussions and key informant interviews)

- Perceptions of program (caretaker acceptability and preferences)
- Sharing and sale of RUTF

The data collection matrices for Kenya and South Sudan can be found in annex.

### 18b. Plans to promote participant retention and complete follow-up

Participants will be given a careful explanation of the importance of completing treatment and have the opportunity to ask any questions prior to enrolment. As described in section 21, all participants will be given the contact information of two local representatives they can approach if they have any feedback for or wish to express any concerns at any time during the study. A health visitor (a community health worker) will follow-up patients who begin to default from treatment (after one week of missed treatment) to assess the reasons for defaulting and help the family strategize on ways to complete to treatment.

If a family chooses not to bring their child back to complete treatment, the child will be discharged as ‘defaulted’ after 3 weeks of missed treatment. No additional data will be collected on children who default.

## Data management

The IRC in Kenya and ACF in South Sudan will use CommCare <https://www.commcarehq.org/home/> to digitally collect all patient info on android tablets. All data will be captured both on paper and digitally, in order to allow for cross-checking of information.

Data on children in the combined protocol will be collected using the OTP patient card, and additional study data will be collected on separate forms for admission, weekly follow-up visits and discharge. Data on children in the standard protocol will be collected using either the OTP or SFP patient card (as appropriate according to anthropometric classification), and additional study data will be collection on separate forms for admission, weekly follow-up visits and discharge. A research officer will be based full-time at each of all 24 health facilities in the study, and will be responsible for entering the information from the patient cards and the additional forms into the CommCare system for each study participant.

Each week, the research coordinator will review all data, and will cross-check a sample of paper forms against the data in CommCare. All discrepancies will be verified against the paper records and the database corrected, as needed. The principal investigator will review the data uploaded into the database on a weekly basis and will follow-up with the research coordinators in Kenya and South Sudan with any questions or concerns.

All patient files will be maintained securely in a locked file throughout the program to ensure patient confidentiality. Unique identifiers will be assigned to each patient and name/address, etc will not be included in the research database used for analysis. The database will be maintained by the PI in a password-protected server hosted by the International Rescue Committee. Only co-investigators (those listed as part of the research team) will have access to the database, with access managed by the PI, until final analyses are complete. After analysis is complete, the final (anonymized) database will be made available on a data repository for further research purposes.

